#### Secondary outcomes

3.1.2

Secondary outcomes include the following: biomechanical parameters, assessed by changes from baseline in patellar tracking using dynamic radiography and three-dimensional gait analysis; pain, measured by the Knee Pain Scale (KPS) (26); joint function, evaluated by the Lysholm Knee Scoring Scale (27, 28); kinetic parameters measured by the IDEEA system during stair climbing, including mean power (W) and pulling acceleration (g); spatiotemporal gait parameters measured by the IDEEA system during stair climbing, including walking speed (m/s), step frequency (steps/min), and double support time (ms); and quality of life, assessed by the 36-Item Short Form Health Survey (SF-36) (29–31).

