#### Inclusion criteria

2.4.1

To be eligible, individuals must (1) be 40 to 60 years of age; The age range of 40–60 years was selected based on a 10-year review of hospital medical records showing that PFPS patients in our setting are predominantly concentrated in this age group. (2) fulfill the clinical diagnostic criteria for patellofemoral pain syndrome (PFPS), including anterior knee pain exacerbated by functional activities (e.g., stair negotiation, squatting), with imaging (x-ray or MRI) confirming no other knee pathologies; and (3) provide written informed consent.

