### Targeted exercise therapy

2.12

A personalized exercise protocol is developed based on the patient's clinical status and physical capacity. The protocol comprises periarticular knee muscle strengthening and joint flexibility exercises to enhance lower extremity stability and optimize knee joint load distribution. Strengthening exercises target the vastus medialis obliquus (VMO) and gluteal muscles, specifically including VMO setting and supine bridging. Flexibility exercises are designed to stretch the tensor fasciae latae (TFL), gluteus medius, hamstrings, and gastrocnemius, specifically including supine cross-body stretch and seated hamstring stretch. Each session lasts 30–60 min and is performed twice daily (morning and evening) over a 6-week period, as 6 weeks is the minimum effective duration and compliance dropped after 6 weeks in our pilot data. The specific interventions are described below.

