#### Statistical analysis

3.2.2

Data will be analyzed using SPSS software (version 26.0, IBM Corp., Armonk, NY, USA). Continuous variables will be presented as mean ± SD, and categorical variables as frequency (n) and percentage (%). The primary outcome is the change in VAS score from baseline to 6 weeks, and an independent samples *t*-test will be used to compare the change scores between the two groups. For outcomes measured at multiple time points (baseline, 6 weeks, 6 months, and 3 years), a linear mixed-effects model will be employed to account for within-subject correlations and to handle missing data under the missing at random assumption, including group, time, and group-by-time interaction as fixed effects and subjects as random effects.

As this is a non-randomized study, baseline characteristics (including age, sex, body mass index, and baseline VAS score) will be compared between groups, and if any significant imbalance is detected, these variables will be included as covariates in the primary analysis to adjust for potential confounding. Secondary outcomes will be analyzed using independent samples *t*-tests for continuous variables and chi-square tests for categorical variables. Missing data will be handled using multiple imputation for sensitivity analysis. A two-tailed *P*-value < 0.05 will be considered statistically significant for all analyses.

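### Patellar tracking is compared as mean change from baseline with no stated normal reference, direction of benefit or baseline adjustment, so on a raw signed measure a significant difference shows a shift, not an improvement

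*Protocol article*

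**What the plan says.** Protocol article, 3.1.2 (Secondary outcomes) lists "biomechanical parameters, assessed by changes from baseline in patellar tracking using dynamic radiography and three-dimensional gait analysis". It names no parameter (shift, tilt, excursion or other), no normal value or range, and no direction that counts as improvement.

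Section 3.2.2 (Statistical analysis) gives the test: "Secondary outcomes will be analyzed using independent samples *t*-tests for continuous variables and chi-square tests for categorical variables". Outcomes measured repeatedly also get a linear mixed model, "including group, time, and group-by-time interaction as fixed effects and subjects as random effects". Both methods compare group means.

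On adjustment, the same section says that "baseline characteristics (including age, sex, body mass index, and baseline VAS score) will be compared between groups". Variables found imbalanced enter the primary analysis, which is VAS. Baseline tracking is not listed, and no adjustment of the tracking outcome is described.

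On entry, 2.4.1 asks patients to "fulfill the clinical diagnostic criteria for patellofemoral pain syndrome (PFPS), including anterior knee pain exacerbated by functional activities (e.g., stair negotiation, squatting" and so on; imaging serves to rule out other knee pathology. Neither 2.4.1 nor 2.4.2 contains a tracking criterion. Section 2.5 allocates by patient preference. Sections 2.5 and 2.8 list biomechanical monitoring for the experimental group only.

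**The concern.** A pain score has a built-in direction: lower is better for everyone. A raw tracking position or angle does not, because improvement means coming closer to normal and the required movement depends on where the knee started. Entry rests on symptoms, and the Introduction calls the etiology multifactorial, so knees with normal and abnormal tracking may both be enrolled. A signed mean change then adds movement toward normal in some patients to movement away from it in others.

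Two misreadings could follow, under different treatment mechanisms. If treatment moves most knees the same way, a significant difference could be reported as better tracking when the average knee is little closer to normal. If treatment instead pulls knees toward normal from both sides, real corrections have opposite signs and a benefit could be missed.

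Preference allocation adds a further reason to use the baseline value. Nothing balances the groups on starting tracking, and change scores alone do not remove the effect of a difference there.

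Tracking is the parameter that the Abstract names for quantification, and the third objective is a biomechanics-guided rehabilitation protocol. A tracking result without a direction gives that objective weak support.

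**Working it through.** **No figure to reproduce.** The protocol gives no effect size, SD or power for tracking. From section 2.6 I take only 43 per group, the number before dropout inflation, as the number analysed. Whether 43 follows from the VAS inputs is a separate question and does not bear on this point.

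**Assumptions (none from the protocol).** The measure is signed, with 0 = normal. A share p of knees starts at +4 mm and the rest at 0 mm, each with SD 1 mm. Follow-up noise has SD 1.5 mm.

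**Illustration A: treatment shifts every treated knee by -2 mm; controls have no shift.**

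1. Signed change. The mean difference is -2 mm and the SD of change is 1.5 mm, so d = 2/1.5 = 1.33. With 43 per group the t-test has power above 0.999, whatever p is.
2. Distance from normal at follow-up. Within each type of knee the SD is s = √(1² + 1.5²) = 1.803. For a normal variable with mean m, the expected absolute value is s·√(2/π)·exp(-m²/2s²) + m·[1 - 2Φ(-m/s)].
   - Control, normal start (m = 0): 1.438 mm
   - Control, off-centre start (m = 4): 4.017 mm
   - Treated, either start (m = -2 or +2): 2.243 mm
3. Effect on distance: normal start 2.243 - 1.438 = +0.804 mm (worse); off-centre start 2.243 - 4.017 = -1.774 mm (better).
4. Average effect = (1 - p)(0.804) + p(-1.774):

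| Share off-centre, p | Signed difference | Change in distance from normal |
|---|---|---|
| 0.3 | -2.0 mm | +0.03 mm |
| 0.5 | -2.0 mm | -0.48 mm |
| 0.7 | -2.0 mm | -1.00 mm |
| 0.9 | -2.0 mm | -1.52 mm |

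The break-even share is 0.804/(0.804 + 1.774) = 0.31. Simulation (4,000 trials per share) agrees to within 0.01 mm. The signed test was significant in 100% of trials at every share, while a benefit on absolute deviation was significant in about 2%, 24%, 73% and 99%.

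**A second set of assumed values** (off-centre start +2, shift -1, baseline SD 0.5, noise SD 1, 3,000 trials) shows the same pattern. The signed test was significant in about 99-100% of trials. Mean change in distance ran from +0.33 with no off-centre knees, through +0.05 at 25% and -0.23 at 50%, to -0.80 at 100%.

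**Illustration B: treatment corrects from both sides.** If a share q deviates one way and 1 - q the other, with equal corrections, the signed mean effect is (2q - 1) times the true effect. Take a true effect of 0.7 SD, 43 per group, and hold the SD fixed:

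| q | Signed effect | Power of signed t-test |
|---|---|---|
| 1.0 | 0.70 SD | 0.89 |
| 0.9 | 0.8 × 0.7 = 0.56 SD | 0.73 |
| 0.7 | 0.4 × 0.7 = 0.28 SD | 0.25 |
| 0.5 | 0 | 0.05 (the test's level) |

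A and B are alternatives and do not operate together.

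**The case against.** The strongest reply is that the protocol names no tracking parameter. It may already be a deviation score, in which case the sign problem disappears, and an article may leave such detail to a fuller document. This stands in part: the point is conditional on a raw signed measure. But the article does fix the outcome as change from baseline and the test as a comparison of means, and nothing in it turns that change into improvement.

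A reader might infer more than the text supports:

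- *That every experimental patient gets an identical programme pushing the patella one way.* Section 2.12 does say "Strengthening exercises target the vastus medialis obliquus (VMO) and gluteal muscles, specifically including VMO setting and supine bridging", but it also calls the protocol personalised to clinical status and physical capacity. Nothing in the article states in which direction the exercises move the patella.
- *That deviation on both sides of normal, or a sizeable share of normal trackers, is established.* The article says neither. It calls the etiology multifactorial but also names dynamic biomechanical dysfunction as the core mechanism of PFPS.
- *That a significant result would probably be misleading.* Illustration A itself shows net improvement at shares of 50% and above. Its near-certain significance follows from an assumed 2 mm between-group shift, although controls do a similar straight-leg raise (section 3).
- *That the objectives fail.* The first objective is to quantify parameters, which needs no between-group test, and the second concerns pain and function.

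A mean and its sign can also be read against baseline values after the fact. That is possible, but a reference chosen once results are known invites a selective reading.

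**Conclusion.** The point holds in conditional form. As written, arms are compared on mean change in tracking without a normal reference, a direction of benefit or baseline adjustment, in patients not selected for abnormal tracking and allocated by preference. On a raw signed measure, significance would then show that tracking shifted, and would not by itself show that it moved toward normal. Opposite corrections would partly cancel.

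The size cannot be fixed from the protocol, because it depends on the unknown mix of baseline tracking. Under the assumed values the same signed result goes with anything from no net gain, at about 31% off-centre, to a gain of about 1.5 mm at 90%. These millimetre figures show the mechanism and are not estimates for this trial.

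The consequence is confined to a secondary outcome and the conclusions drawn from it. The change should be made before data are seen, but nothing here affects the VAS comparison.

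**What to change.** In 3.1.2, before data are seen, name the tracking parameter, its normal reference and the direction that counts as improvement. Where the parameter can err on both sides, score it as deviation from that reference. The choice of reference belongs to the investigators, since the article documents none.

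In 3.2.2, compare arms on follow-up tracking adjusted for its baseline value. Add the arm-by-baseline interaction as an exploratory supporting analysis, as the study is not sized for it. Report the signed change descriptively.

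Also make clear that tracking is measured at the same visits in both groups. Sections 2.5 and 2.8 list biomechanical monitoring only for the experimental group, and a between-group comparison needs both.

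Cost: a few sentences and one derived variable. If the control group's imaging is already planned, no further patients or examinations are needed; if it is not, that must be settled first. Downsides: a reference must be chosen in advance, a deviation score is skewed and inflated by measurement noise near zero, and the effect may look smaller than the raw shift.

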#### Control of expectation bias

3.1.3

Because the primary outcome is measured using the Visual Analog Scale (VAS), a patient-reported instrument, patients’ treatment expectations may influence their scores and thus introduce expectation bias. To address this issue, we will record patients' treatment expectation scores (on a 0–10 scale) at baseline and compare them between the two groups. If a significant difference exists between the groups, the expectation score will be included as a covariate in sensitivity analyses to adjust for its potential effect on the primary outcome.

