**Methods and analysis:**

This single-centre, prospective, interventional cohort study will investigate the effectiveness of a biomechanically monitored targeted exercise protocol combined with Traditional Chinese Medicine (TCM) compared with conventional exercise combined with TCM in patients with patellofemoral pain syndrome (PFPS). We will consecutively recruit 96 eligible patients. Participants will be assigned to either an experimental group or a control group based on their preference after receiving standardized information. The experimental group will receive biomechanical monitoring, targeted exercise, and Traditional Chinese Medicine (TCM), whereas the control group will receive conventional exercise and the same TCM regimen.

Outcomes will be assessed at baseline, 6 weeks, 6 months and 3 years post-intervention. The primary outcome measure will be pain intensity measured using the Visual Analog Scale (VAS). Secondary outcome measures will include: biomechanical parameters; pain (Knee Pain Scale); joint function (Lysholm Knee Scoring Scale); kinetic parameters (mean power and pulling acceleration during stair climbing using the IDEEA system); spatiotemporal gait parameters (walking speed, step frequency, double support time during stair climbing using IDEEA); and quality of life (36-Item Short Form Health Survey).

For statistical analysis, independent samples *t*-tests will be used for between-group comparisons, and linear mixed-effects models will be applied for outcomes measured at multiple time points. To control for expectation bias, patients' treatment expectation scores will be recorded at baseline and adjusted as covariates if significant between-group differences exist. Baseline characteristics will be compared, and any imbalanced variables will be included as covariates in the primary analysis. A two-tailed *P*-value < 0.05 will be considered statistically significant.

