### Group allocation and intervention

2.5

Patients will be assigned to either the experimental group or the control group based on their preference after receiving standardized information about both interventions. Specifically, the experimental group will receive biomechanical monitoring, targeted exercise, and Traditional Chinese Medicine (TCM), whereas the control group will receive conventional exercise and the same TCM regimen as the experimental group.

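### Section 3.1.3 keeps treatment expectation out of the primary VAS analysis even when the self-selected groups differ on it; the Abstract sets no such limit, and both adjust only after a significant baseline test

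*Protocol article*

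**What the plan says.** All references are to the protocol article.

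- **Allocation (2.5).** Patients enter a group "based on their preference after receiving standardized information about both interventions". They therefore know their treatment when they score the primary outcome, a self-reported 0-10 VAS (3.1.1).
- **Expectation, 3.1.3.** The section explains that "treatment expectations may influence their scores and thus introduce expectation bias". It records a 0-10 expectation score at baseline, compares it between groups, and then states: "If a significant difference exists between the groups, the expectation score will be included as a covariate in sensitivity analyses".
- **Expectation, Abstract.** Here "treatment expectation scores will be recorded at baseline and adjusted as covariates if significant between-group differences exist". No analysis is named. The next sentence but one clause concerns baseline characteristics in general: "any imbalanced variables will be included as covariates in the primary analysis".
- **Covariates, 3.2.2.** The main comparison at 6 weeks is unadjusted by default: an "independent samples *t*-test will be used to compare the change scores between the two groups". The groups are also to be checked on baseline variables, with age, sex, BMI and baseline VAS given as examples. The rule that follows from this check is: "if any significant imbalance is detected, these variables will be included as covariates in the primary analysis". Expectation is not among the named examples.

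**The concern.** In a preference-allocated, unblinded comparison with a self-reported outcome, a patient's belief in a treatment can plausibly affect both which arm is chosen and how pain is scored afterwards. That makes expectation a confounder of the primary contrast, and the protocol recognises it as a threat.

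Two faults follow from the text.

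1. **Role.** Under 3.1.3 a demonstrated imbalance in expectation changes only a sensitivity analysis. Under 3.2.2 a demonstrated imbalance in BMI or sex changes the primary analysis. The Abstract does not limit expectation in the way 3.1.3 does. An analyst could defend either model, and could do so after seeing the results.
2. **Trigger.** Both places make adjustment depend on a significant baseline difference. A non-significant test with 48 per group does not show that confounding is absent, and when it occurs expectation enters no analysis at all.

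At stake is whether a between-group VAS difference reflects the treatment or the beliefs of those who chose it.

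**Working it through.** **Inputs from the protocol (2.6):** SD 2.0 VAS points, planned difference 1.1 SD = 1.1 × 2.0 = 2.2 points, two-sided alpha 0.05, 43 per group before and 48 per group after allowance for dropout. The plan gives no figure for expectation bias, so there is none to reproduce on this point. (The 43 does not follow from the stated formula: 2 × ((1.960 + 1.645)/1.1)² = 21.5, so 22 per group. That is a separate matter and nothing below depends on it.)

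**Assumptions not in the documents:** true baseline difference in expectation of k SD; within-group correlation r between expectation and VAS change; no treatment effect; normal data; equal groups.

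**Step 1: how often the gate opens.** P(p < 0.05) ≈ Φ(k/√(2/48) − 1.96) + Φ(−k/√(2/48) − 1.96), with √(2/48) = 0.204.

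- k = 0.2: 16%
- k = 0.3: 0.3/0.204 = 1.47, so 31% (shut 69%)
- k = 0.4: 0.4/0.204 = 1.96, so 50%
- k = 0.5: 69%

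Preference need not produce equal groups. With a 24/72 split the gate opens less often: 25% at 0.3 SD and 40% at 0.4 SD.

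**Step 2: bias and type I error if expectation is left out (the 3.1.3 reading).** Bias ≈ r × k × SD.

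- Low end: 0.3 × 0.2 × 2.0 = 0.12 points
- High end: 0.5 × 0.5 × 2.0 = 0.50 points

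The standard error of the difference is 2.0 × 0.204 = 0.408. The ratios are 0.12/0.408 = 0.29 and 0.50/0.408 = 1.22, and the normal approximation gives type I errors of about 6% and 23%.

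**Step 3: simulation, 48 per group, 5,000 trials per setting.** Cells show bias in VAS points / type I error.

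| k (SD) | r | Left out (3.1.3) | Gated, in main analysis | Always adjusted |
|---|---|---|---|---|
| 0.2 | 0.3 | 0.122 / 5.9% | 0.074 / 5.0% | 0.003 / 4.9% |
| 0.2 | 0.5 | 0.195 / 8.1% | 0.117 / 5.7% | −0.005 / 5.9% |
| 0.3 | 0.3 | 0.173 / 7.1% | 0.072 / 5.3% | −0.010 / 5.0% |
| 0.3 | 0.5 | 0.303 / 11.5% | 0.134 / 6.0% | 0.000 / 5.0% |
| 0.4 | 0.3 | 0.235 / 8.8% | 0.071 / 5.7% | −0.003 / 5.0% |
| 0.4 | 0.5 | 0.396 / 15.9% | 0.119 / 5.9% | −0.004 / 5.1% |
| 0.5 | 0.3 | 0.297 / 11.0% | 0.053 / 5.5% | −0.003 / 5.0% |
| 0.5 | 0.5 | 0.497 / 23.4% | 0.087 / 6.4% | 0.000 / 5.6% |

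The Monte Carlo standard error near 5% is √(0.05 × 0.95/5000), about 0.3 percentage points.

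**Step 4: larger imbalances, expectation left out, 43 per group, r = 0.3 (6,000 trials).** At k = 0.8 the bias is 0.242 × 2.0 = 0.48 points and the type I error 20%. At k = 1.0 they are 0.298 × 2.0 = 0.60 points and 28%.

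**Step 5: price of adjusting.** With equal groups the variance inflation from the group-expectation correlation is 1 + k²/4: 1.06 at 0.5 SD, 1.16 at 0.8 SD, 1.25 at 1.0 SD. Adjustment also multiplies residual variance by 1 − r², which is 0.91 at r = 0.3. The net variance factors are then 1.0625 × 0.91 = 0.97, 1.16 × 0.91 = 1.06 and 1.25 × 0.91 = 1.14.

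**The case against.** Four points can fairly be made for the plan.

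- **The contradiction is softer than it looks.** A reader might infer that the Abstract places expectation in the primary analysis. Its sentence on expectation names no analysis; the words about the primary analysis come in the following sentence, on baseline characteristics. Section 3.1.3 could be the detail behind a condensed abstract. This stands: what is established is that one place limits the adjustment and the other does not.
- **Section 3.2.2 does not exclude expectation.** A reader might take its list as closed. It is introduced as a set of examples, and expectation is a baseline score. This stands too, but it does not settle the matter: if 3.2.2 covers expectation, it sends an imbalanced score to the primary analysis and conflicts with 3.1.3 directly.
- **The gate alone does little to type I error.** A reader might attach the 20% to 28% to both versions of the rule. Gated adjustment in the main analysis gives 5.0% to 6.4% at imbalances of 0.2 to 0.5 SD, and at 0.8 SD or more the gate opens about 97% of the time or more with 48 per group. The large figures belong to 3.1.3 alone, and there an adjusted sensitivity result would usually appear beside the primary one. This stands. What remains against the gate is a residual bias of about 0.05 to 0.13 points, and the trials in which nothing is adjusted.
- **The bias is modest against the planned effect.** The largest value shown, 0.60 points, is 0.60/2.2 = 27% of the planned difference. A reader might infer that expectation could account for an effect of the planned size; these figures do not support that. They do show a materially raised false-positive risk when there is no true effect.

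**Conclusion.** The point holds as a should-fix. The Abstract, 3.1.3 and 3.2.2 do not give expectation one clear role. Followed literally, 3.1.3 leaves in the primary estimate a bias that the same section identifies, even after imbalance has been demonstrated.

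How much this matters depends on two quantities the documents do not give, the imbalance and the correlation. Over the ranges examined, the false-positive risk under 3.1.3 runs from barely above nominal to several times nominal. The direction is also an assumption: the bias favours the monitored arm only if patients with higher expectations choose it and higher expectation goes with a better reported pain change.

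The near-zero bias after full adjustment holds within the simulated model, where expectation is measured without error, acts linearly and is the only confounder. It should not be read as a promise that adjustment removes all bias from self-selection.

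**What to change.** 1. Replace the unadjusted t-test as the primary 6-week analysis with a linear model (ANCOVA) containing group, baseline VAS and the baseline expectation score for every patient, whatever the baseline p-values.
2. Report the same model without expectation as the sensitivity analysis.
3. Word the rule identically in the Abstract, 3.1.3 and 3.2.2, before outcome data exist (2.2 schedules the start for June 2026).

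Optionally, record the 0-10 expectation for each of the two treatments after the standardised information and before the patient chooses, so that the score does not reflect a choice already made.

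**Cost.** The expectation score is already collected, so the core change needs no new data. It is nevertheless a change of primary method and not only of wording. It uses one model degree of freedom for expectation and carries a variance inflation of about 1.06 to 1.25 if the groups differ by 0.5 to 1.0 SD. At a correlation of 0.3 the adjusted estimate is slightly less precise from 0.8 SD upwards. Confounding from other reasons for choosing an arm, and from measuring expectation with a single item, remains and should be acknowledged in the report.
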